**Methods:**

A three-arm, randomized superiority clinical trial with a pre-post and repeated follow-up measures intergroup design using a 1:1:1 allocation ratio will be performed. One hundred and twenty-three cancer survivors with mild to moderate cognitive impairment will be randomly assigned to one of the study interventions: a cognitive rehabilitation intervention group, an intervention group with UP intervention, or a control group on the waiting list. The primary outcome is to observe a significant improvement in cognitive function in both intervention groups and a significant decrease in emotional impairments in comparison with the waitlist group. Improvements in anxiety, depression, and quality of life are also expected as secondary outcomes. These results will be maintained at 6 months of follow-up.

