### Trial design {8}

This is the protocol of a three-arm, controlled, randomized superiority trial, with a pre-post and repeated follow-up measures intergroup design. Participants with mild to moderate cognitive impairment will be randomly assigned to group 1: Unified Protocol for Transdiagnostic Treatment of Emotional Disorders (UP) intervention, group 2: Neuropsychological intervention, or group 3: Waitlist control group. For ethical reasons, the participants in group 3 will be offered the option to receive the neuropsychological intervention. The evaluation will be carried out at three time points: an initial evaluation prior to randomization (pre-treatment; T0), at the end of the intervention (post-treatment; T1), and at 6 months after completing the intervention (T2) (see Fig. 1).

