### Intervention description {11a}

Unified Protocol for the Transdiagnostic Treatment of Emotional Disorders (UP). The UP intervention will focus on a deficit in emotional regulation common to all emotional disorders (ED). Specifically, the intervention will address the adaptive value of emotions and promote tolerance to intense emotions as well as identify and modify dysfunctional emotional regulation strategies. Patients will receive 8 group therapy sessions (8–10 cancer survivors per group) with all UP modules [20]. The Spanish version of the therapist’s guide and the patient’s workbook will be used [21]. All patients will receive the workbook to inform them of the contents of each session, aid them in doing the recommended exercises between sessions, and help them once the treatment is completed. The treatment will last 8 weeks (one session per week) as follows:*Session 1: Motivation for change and commitment to treatment.* The main objectives of the first session are to establish the therapeutic relationship and promote motivation for change. Therefore, tasks pursuing that goal will be carried out such as the analysis of the advantages and disadvantages of change and the setting of treatment goals or life goals.*Session 2*: *Understanding emotions.* The second session will focus on teaching the adaptive components of emotions in patients and will begin by working with the concept of emotion-driven behaviors (EDBs), differentiating between three emotional components: behaviors, thoughts, and physical reactions.*Session 3: Emotional awareness training. Learning how to observe experiences.* In this session, patients will be trained in emotional awareness through the practice of exercises focusing on the present without judging what they are perceiving. For example, exercises involving mood induction with music.*Session 4: Cognitive restructuring.* The objective of this session is to promote cognitive flexibility. To achieve this aim, participants will be trained to identify and modify non-adaptive thoughts (e.g., through cognitive restructuring or positive self-instruction).*Session 5: Emotional avoidance and EDBs.* This session will analyze emotional avoidance patterns and EDBs as well as their role in the development and maintenance of emotional disorders. In addition, patients will be trained to modify their dysfunctional behaviors.*Session 6: Physical sensations tolerance.* In this session, the objective is to train patients in improving their tolerance to physical sensations. To this end, participants will learn to identify uncomfortable inner physical sensations associated with emotions using breathing exercises.*Session 7: Situational and interoceptive emotional exposure.* The objective of this session is to expose the patient to emotions by promoting habituation instead of emotional avoidance. A situational and emotional avoidance hierarchy will be developed and followed by exposure exercises for that purpose.*Session 8: Maintenance of treatment gains and relapse prevention.* In the last session, participants will check their progress and what was learned in previous sessions will be recapitulated to promote the later use of this knowledge once the intervention is over. The aim is to provide patients skills to deal with demanding situations in the future.

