The intervention will be carried out in groups with a maximum of 5 participants per group [17] and consists of 8 weekly sessions of 2 h each: the first hour for memory training and the second for processing speed exercises (PSE). Contents for 8 weeks:*Session 1: Clustering strategies and PSE.* In the first session, the goal is to learn how to organize a list of verbal or visual stimuli into meaningful categories and clustering during the first hour. To achieve this goal, the psychologist will introduce the session and explain the strategies and exercises to practice them. In the second hour of the session, the participants will be trained in processing speed using the InSight program. The psychologist will remain in the room to answer any questions and support the participants while they do the computerized exercises.*Session 2*: *Summarizing strategies and PSE.* In the first hour of this session, participants will be trained to organize, summarize, and select the main ideas and details in order to remember text-based information. Once the strategies have been explained, paper-based exercises will be used. Later, patients will do processing speed exercises on computers under the psychologist’s supervision.*Session 3*: *Visualizing strategies and PSE.* The first hour of the third session focuses on teaching visualizing strategies to remember different items. In the same line as previous sessions, the strategy will be explained first and the practical exercises will be performed later. The second hour will focus on processing speed exercises using the Posit Science InSight program as well.*Session 4*: *Association strategies and PSE.* In the first hour of this session, the objective is to use association to remember items. In this case, the strategies will be taught using both visual and verbal materials. In the second hour, participants will be trained in processing speed as usual with the psychologist’s support when necessary.*Sessions 5, 6, 7, and 8: Revising strategies and PSE.* In the last four sessions, what was learned in the previous sessions will be entrenched with additional practice exercises in the first hour. Thus, mixed exercises will be done in these sessions where participants are asked to apply different strategies to each exercise and solve doubts. Likewise, processing speed training with the Insight program will be provided in the second hour.

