### Sample size {14}

The sample size has been estimated based on data obtained in a similar randomized trial with cancer patients of different types [12]. This study examined the effect of a cognitive rehabilitation program on cognitive impairment compared to a control group. The results showed a moderate effect size of 0.49 at post-treatment. Given these results, a medium effect size of 0.5 (*d* index) has been assumed to detect differences between the interventions and the waitlist group. Because no software was available to determine the sample size for linear mixed model analyses, we used the *f* index of G*Power. Therefore, an effect size of 0.25 (*f* index) is assumed, equivalent to *d* = 0.5. Thus, with a statistical power of 0.80, an alpha level of 0.05, a correlation between repeated measures of 0.5 and three groups, a total sample of 108 participants (36 participants in each group) is required. Previous studies have reported a participant withdrawal rate of around 13% [12]. Therefore, assuming this withdrawal rate, the total sample would be 123 participants, 41 per group.

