## Statistical methods

### Statistical methods for primary and secondary outcomes {20a}

The obtained data will be analyzed following the intention-to-treat (all randomized patients are included in the analysis) and per protocol (only patients with post-treatment assessment are included in the analyses) approaches. In an intention-to-treat analysis, incomplete or missing data will be considered using the maximum likelihood estimation method. First, ANOVA or chi-square tests will be performed to compare the demographic variables and outcome measures at baseline (T0). Second, to examine longitudinal changes over time (baseline, post-treatment, and follow-up) and between-group differences in the mentioned variables, mixed linear models will be used, since these models are more precise than repeated measures ANOVA [41]. The Friedman test will be performed to analyze a potential group-level effect among participants receiving the intervention together. In addition, Cohen’s *d* with bias corrections will be calculated to determine the effect size of the between-group comparisons. The most important analysis will be performed between the two active groups (the neuropsychological treatment group and the transdiagnostic treatment group) and the control group, as well as a comparison between both active groups to observe the evolution of cognitive deficits, anxiety-depressive symptoms, and quality of life of the participants just after the application of the interventions and at 6 months of follow-up. Once the analyses are performed, summary tables will be provided for all the planned evaluations: baseline (T0), end of treatment (T1), and follow-up at 6 months (T2). The results will be presented in the form of frequency tables and by means of descriptive statistics (the mean, standard deviation, and percentages) to summarize the characteristics of both the total sample and the participants in each of the three groups. Finally, the results of the study will be reported in accordance with the 2010 statement of the Consolidated Standards of Reporting Trials (CONSORT) [42] and the 2013 guidelines for Standard Protocol Items: Recommendations for Interventional Trials (SPIRIT) [43].

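### The 80% power in Sample size {14} assumes independent participants although both active treatments are given in therapy groups; the shortfall depends on an unstated ICC and is largest for UP

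*Protocol article*

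**What the plan says.** Sample size {14} of the protocol article states a complete calculation: "an effect size of 0.25" on the f index, "with a statistical power of 0.80, an alpha level of 0.05, a correlation between repeated measures of 0.5 and three groups". From this it concludes that "a total sample of 108 participants (36 participants in each group) is required", and a withdrawal rate of about 13% raises the total to 123, or 41 per arm. No ICC, design effect or therapy-group size is among the inputs.

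Intervention description {11a} sets out how the treatments are given. For UP: "Patients will receive 8 group therapy sessions (8–10 cancer survivors per group". For the neuropsychological treatment: "The intervention will be carried out in groups with a maximum of 5 participants per group". The waitlist has usual care, with no therapy groups, while the two active arms are being treated.

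Statistical methods {20a} plans a Friedman test for "a potential group-level effect among participants receiving the intervention together". The authors therefore recognise possible dependence at the analysis stage, but the planning figure takes it as zero.

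**The concern.** People treated together share a therapist, a schedule and each other's company, so their outcomes may be correlated. Any positive correlation raises the variance of that arm's mean by 1 + (m − 1) × ICC, where m is the number of participants per group. The arm is then worth fewer than 36 independent people, and its mean rests on a handful of independent units.

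The effect differs by arm: largest in UP, smaller in the neuropsychological arm, and absent in the ungrouped waitlist. UP is the treatment named in the primary objective, and the first hypothesis is UP against neuropsychological treatment, where both arms are grouped. The Discussion also lists the sample-size estimate as a strength, so readers will rely on it. If power for UP is lower than stated, a null result would be given more weight than it deserves.

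**Working it through.** **1. Reproduce the plan's figure.** Inputs from Sample size {14}: f = 0.25, alpha = 0.05, r = 0.5, k = 3 groups. From Trial design {8}: "The evaluation will be carried out at three time points". The abstract gives equal arms: "using a 1:1:1 allocation ratio". For a repeated-measures between-factor F test:

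λ = f² × N × 3 / (1 + 2r) = 0.0625 × 108 × 3 / 2 = 10.125, with df (2, 105).

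Power is 0.809 at N = 108 and 0.797 at N = 105, so 108 is an exact match under independence.

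**2. Number and size of therapy groups.**
- UP: 41/10 = 4.1 and 41/8 = 5.1, so 5 groups. Evaluable per group: 36/5 = 7.2.
- Neuropsychological: 41/5 = 8.2, so at least 9 groups. Evaluable per group: 36/9 = 4.

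**3. Design effects.** The documents give no ICC; 0.01 to 0.10 is an assumption. UP: 1 + 6.2 × ICC. Neuropsychological: 1 + 3 × ICC. Waitlist: 1.

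| ICC | UP | Neuropsychological |
|---|---|---|
| 0.02 | 1.12 | 1.06 |
| 0.05 | 1.31 | 1.15 |
| 0.10 | 1.62 | 1.30 |

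At ICC 0.05, 36 participants are worth 36/1.31 = 27.5 in UP and 36/1.15 = 31.3 in the neuropsychological arm.

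**4. Power of the plan's own omnibus test.** The mean of three measurements at r = 0.5 has variance 2/3, so each arm has weight w = 36/(2/3 × DE) = 54/DE. Then λ = Σ w(μ − weighted mean)², with the means scaled to f = 0.25. Because the arms now differ in variance, the answer depends on which means differ.

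Worked case, ICC 0.05: the weights are 41.2, 47.0 and 54. When one arm differs from two equal arms, f = 0.25 means a difference δ with δ² = 0.0625 × 4.5 = 0.281.
- Only UP differs: λ = 0.281 × 41.2 × 101.0 / 142.2 = 8.23, power 0.718.
- Both active arms equal and different from waitlist: λ = 0.281 × 54 × 88.2 / 142.2 = 9.42, power 0.778.

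| ICC | Active arms equal, differ from waitlist | Equally spaced (UP, neuropsychological, waitlist) | Only UP differs |
|---|---|---|---|
| 0 | 0.809 | 0.809 | 0.809 |
| 0.01 | 0.802 | 0.796 | 0.790 |
| 0.02 | 0.796 | 0.784 | 0.771 |
| 0.05 | 0.778 | 0.749 | 0.718 |
| 0.10 | 0.749 | 0.697 | 0.639 |

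These keep df (2, 105); degrees of freedom based on therapy groups would lower them further.

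**5. Pairwise contrasts at one time point, for illustration.** d = 0.5, 36 per arm, ICC 0.05, variance (DE₁ + DE₂)/36, noncentral t. The protocol assumes d = 0.5 only against the waitlist; using it for UP against neuropsychological is an assumption. Group-based df are Satterthwaite, from 5 − 1 and 9 − 1 groups and 36 − 1 waitlist participants.

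| Contrast | No clustering | ICC 0.05, 70 df | ICC 0.05, group-based df |
|---|---|---|---|
| UP v waitlist | 0.553 | 0.495 (variance 2.31/36) | 0.441 (df 11.7) |
| UP v neuropsychological | 0.553 | 0.471 (variance 2.46/36) | 0.410 (df 10.2) |
| Neuropsychological v waitlist | 0.553 | 0.523 (variance 2.15/36) | 0.501 (df 23.8) |

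**The case against.** **The loss may be small.** This stands in part. No ICC is documented. At 0.01 omnibus power is 79–80%, and at 0.02 with both active arms equal it is 79.6%. A reader might infer that the trial simply fails to deliver 80%; the documents support that only conditionally on the ICC.

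**UP has five groups, not four.** This stands. Dividing 36 evaluable participants by 9 suggests four groups, but the protocol randomises 41 with at most 10 per group, so five are needed at the start. Pairing the evaluable 36 with full starting groups overstates the design effect (1.40 instead of 1.31 at ICC 0.05).

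**The low pairwise power is mostly another matter.** This stands. A reader might attribute all of the low pairwise power to clustering. The 55% starting point exists without any clustering: it comes from treating f = 0.25 across three groups as the same as a pairwise d = 0.5, and from using a single time point. {20a} plans mixed models on all time points, not that t test. Adjusting for baseline at r = 0.5 would start from about 68%. What clustering adds for UP against waitlist at ICC 0.05 is about 6 points through variance and about 5 more through degrees of freedom.

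**G*Power is openly a stand-in, and the analysis addresses the group effect.** This does not rescue the figure. Lack of mixed-model software does not prevent applying a design effect. The Friedman test compares repeated measures within blocks; it neither estimates a therapy-group variance nor corrects a standard error. No later analysis plan can make a planning power true that rests on independence.

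**Restating power restores none.** True, and recruitment had begun by publication. But the stated figure governs how a null result is read.

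**Conclusion.** The point holds in a conditional form. The protocol's 80% is correct arithmetic on a premise of independence that its own delivery format puts in doubt and its own analysis section does not take for granted. With 5 UP and 9 neuropsychological groups, omnibus power is about 77–80% at ICC 0.02, 72–78% at 0.05 and 64–75% at 0.10, against 81% under independence. The high end applies if the two active arms are equal and differ from waitlist, the low end if only UP differs. The loss is negligible at ICC 0.01 and greatest for contrasts involving UP.

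These figures assume the ICC range, equal group sizes, a design effect applied to the average over all three measurements although T0 precedes treatment, and an ungrouped waitlist. The last is safe up to T1 but less so at T2, because the waitlist is due to receive the group-based neuropsychological treatment once the active arms finish.

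**What to change.** Keep the 123 participants and restate Sample size {14}:
- name an assumed therapy-group ICC with a range, for example 0.02 to 0.10, labelled as an assumption;
- apply 1 + (m − 1) × ICC to the UP and neuropsychological arms and 1 to the waitlist;
- give the expected numbers of therapy groups, about 5 and 9;
- state the pattern of arm means behind f = 0.25;
- base degrees of freedom on therapy groups;
- report the resulting power range, for the omnibus test and for the UP contrasts, in place of an unqualified 80%.

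The cost is one paragraph and a short calculation, with no extra participants. The downside is a less favourable stated power; the change makes the figure honest but does not raise it.

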### Recruitment {15}

The oncology team at the Reina Sofia University Hospital of Cordoba (Spain) will be responsible for assessing the suitability of the patients to enter into the study during their routine visits, based on their clinical histories and following the inclusion and exclusion criteria. Eligible participants will be contacted using a telephone by a member of the research team with formation in clinical psychology to provide an invitation to participate in the study. It is expected that a sufficient number of participants will be recruited to start the different interventions with the same number of participants at the same time.

## Assignment of interventions: allocation

### Sequence generation {16a}

Participants who obtain scores indicating mild or moderate cognitive deterioration will be randomly assigned to one of the three interventions (Neuropsychological treatment/Unified Protocol for the Transdiagnostic Treatment of Emotional Disorders (UP)/waitlist group) at a 1:1:1 ratio using a computer-generated set of numbers (https://www.randomizer.org/) and stratified by psychiatric medication and fibromyalgia diagnosis (if any).

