#### .Demographic Variables Questionnaire

This questionnaire was prepared by the researchers of this work to collect some sociodemographic and clinical variables that are intended to be analyzed such as age, sex, marital status, level of education, psychiatric medication (if any), type of cancer and cancer stage, kind of cancer treatment, time from cancer diagnosis to end of chemotherapy, and fibromyalgia diagnosis.

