## Discussion

Cancer patients frequently develop cognitive impairments that negatively affect their quality of life and functional status, especially those who have undergone chemotherapy [3–5]. Several psychological interventions to reduce the frequency of these cognitive alterations have shown positive results. However, a relationship has been observed between emotional well-being (anxiety and depression) and the severity of cognitive alterations in these patients. Therefore, a transdiagnostic intervention can be useful to improve their emotional state and cognitive performance [8–16].

This protocol includes information on a randomized controlled trial in which an intervention based on Barlow’s Unified Protocol (UP) will be carried out with the aim of improving the emotional state and cognitive performance of cancer patients. The UP intervention will be compared to a well-established neuropsychological intervention and a waiting list group. The group assigned to the transdiagnostic intervention group is expected to obtain significantly better outcomes in cognitive performance, anxiety, depression, and quality of life compared to the other two groups.

The planned trial has certain strengths that deserve mention. First, it will include a significant number of participants after estimating the sample size necessary to obtain relevant results. Furthermore, using a randomized controlled trial is an advantage of this protocol, as well as the inclusion of a waitlist control group with which to compare the results. Finally, the intervention based on the transdiagnostic model can help not only to improve the cognitive performance of the participants, but also their emotional state.

Finally, it is necessary to mention some limitations foreseen in this trial. The different treatments which the participants will undergo may influence the results. In addition, differences in the time from completion may influence the participants’ outcomes, although the effect of time on the results is expected to be controlled. Finally, the inclusion of patients with breast cancer only may limit the usefulness of the results, since cognitive alterations appear in cancer patients in general.

Despite these limitations, the expected results of this randomized and controlled trial can help to achieve a comprehensive improvement in cancer patients in relevant areas such as cognitive function and emotional state.

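### The analysis text states neither a baseline constraint nor use of the randomization strata, and the expected control for time since chemotherapy has no matching term in the model

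*Protocol article*

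**What the plan says.** All references are to the protocol article.

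- **Sequence generation {16a}:** allocation is 1:1:1 and "stratified by psychiatric medication and fibromyalgia diagnosis (if any").
- **Statistical methods {20a}:** for change across baseline, post-treatment and follow-up, and for differences between groups, "mixed linear models will be used, since these models are more precise than repeated measures ANOVA". Before that, "ANOVA or chi-square tests will be performed to compare the demographic variables and outcome measures at baseline (T0"). No covariate, stratification factor or constraint on baseline means is named. None is excluded either.
- **Primary outcomes {12}:** effects are framed as T1 relative to T0.
- **Trial design {8}:** T0 is measured before randomization.
- **Discussion:** after noting that differences in time from completion may influence outcomes, it adds that "the effect of time on the results is expected to be controlled". It does not say how.
- **Demographic Variables Questionnaire:** the only interval named is "time from cancer diagnosis to end of chemotherapy". The list is given as examples.
- **Eligibility criteria {10}:** patients are excluded if the last chemotherapy session was less than 6 months or more than 6 years ago.

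**The concern.** Two things are at stake.

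The first is precision. T0 precedes randomization, so the true arm means at T0 are equal by design. A model that estimates them separately, and then takes the difference in change from T0, spends information on a difference known to be zero. The plan's text, with T0 as a modelled visit and effects expressed relative to T0, is most naturally run in that way. Its own correlation of 0.5 shows that the loss would not be trivial. The strata raise a related, smaller point: factors used to restrict the randomization should normally appear in the analysis, and the methods do not mention them.

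The second is consistency. The Discussion relies on control of time from completion as the answer to a limitation it raises itself. The Background treats that time as prognostic: it cites impairment in 71% after chemotherapy and 61% six months after completion, and evidence of improvement after six months. Yet the model described has no term for it, and the interval named for collection ends where the relevant interval begins.

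**Working it through.** **Inputs.** From Sample size {14}: "an alpha level of 0.05", "with a statistical power of 0.80", "an effect size of 0.25" for f (taken as d = 0.5), correlation r = 0.5, three groups, 36 per group. From Trial design {8}: three visits. Values of r other than 0.5 and all explained-variance figures below are assumptions.

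**1. The plan's own figure.** For a repeated-measures ANOVA, between-group factor, with m = 3 visits:

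lambda = f² × N × m / [1 + (m-1)r] = 0.0625 × 108 × 3 / 2 = 10.125, df = (2, 105).

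Power is 0.809 at N = 108 and 0.797 at N = 105, so 108 reproduces. It is the sample size for an omnibus group effect averaged over all three visits. It uses no covariates and does not depend on the strata.

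**2. One active arm against waitlist at T1.** With unit variance and n per arm, the contrast has variance (2/n) × k, where

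- k = 2(1-r) for the change from T0 with free T0 means;
- k = 1-r² with T0 means constrained equal, or T0 as a covariate.

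At r = 0.5, k is 2 × 0.5 = 1.00 against 1 - 0.25 = 0.75. An unadjusted comparison at T1 alone also has k = 1. The standard error ratio is √0.75 = 0.866, about 13% smaller, and 1/0.75 = 1.33 in sample size.

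Power at d = 0.5, n = 36, two-sided 0.05, 70 df, uses noncentrality d/√(2k/n):

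- k = 1.00: 0.5/√(2/36) = 2.12, power 0.55;
- k = 0.75: 0.5/√(1.5/36) = 2.45, power 0.68.

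| r | k, free T0 | k, constrained or adjusted | Power, free | Power, constrained or adjusted |
|---|---|---|---|---|
| 0.3 | 1.40 | 0.91 | 0.42 | 0.59 |
| 0.5 | 1.00 | 0.75 | 0.55 | 0.68 |
| 0.7 | 0.60 | 0.51 | 0.77 | 0.83 |

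**3. What strata and time since chemotherapy add.** The documents do not give the variance these explain. Suppose they explain a share q equally at T0 and T1. Both variances become 1-q and the covariance becomes 0.5-q, so the residual variance given T0 is (1-q) - (0.5-q)²/(1-q).

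- q = 0.05: 0.95 - 0.45²/0.95 = 0.737; 0.75/0.737 = 1.018, about 2% of sample size.
- q = 0.10: 0.90 - 0.40²/0.90 = 0.722; 0.75/0.722 = 1.038, about 4%.

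In an unadjusted change contrast, effects that are the same at T0 and T1 cancel within person, so adding the strata there would gain essentially nothing.

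**4. The time variable.** The Discussion concerns completion of treatment to assessment. The questionnaire names diagnosis to end of chemotherapy. Adjusting for the second does not control the first. Eligibility screening uses the last chemotherapy session, so the needed interval must be known for each participant.

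**The case against.** The strongest reply is that silence is not a decision. Covariate lists and the parameterisation of baseline are commonly left to an analysis plan, which is not shown, and a condensed article need not carry them. T0 as a modelled visit fits a constrained or an unconstrained model. This stands. A reader might infer that the trial has decided to ignore the strata and leave T0 free; the documents do not say so, and the loss in step 2 is conditional on that choice. What remains is that the text as written leads naturally to the less efficient contrast, and that one sentence would prevent it.

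A reader might also infer that control for time since chemotherapy cannot be done, or that it depends on the questionnaire's interval. Neither follows. The Discussion ties the control to no variable, the questionnaire list is illustrative, and the interval can be derived from eligibility data. The mismatch between the sections nevertheless remains.

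It is also tempting to add a further 5-11% of sample size for strata and time, from 1/0.95 and 1/0.90. That largely double-counts, because T0 already carries much of their signal; step 3 gives about 2-4%. The medication stratum may also be small, since the eligibility criteria exclude mental disorder before the cancer diagnosis and several drug classes.

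Finally, the baseline significance tests are uninformative after randomization, but nothing says they select covariates. They cost no precision.

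**Conclusion.** The point holds in a limited form. If the mixed model is run with free T0 means, each pairwise contrast of change to T1 has one third more variance than it needs at the plan's r = 0.5, and power of 0.55 rather than 0.68 at d = 0.5 with 36 per arm. The gain is larger at r = 0.3 and smaller at r = 0.7. These figures assume equal variances at T0 and T1, complete data and a two-sided 0.05 test of one pair of arms. They do not contradict the stated power of 0.80, which belongs to a different, omnibus test.

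The mismatch over time from completion needs no assumption: the Discussion, the methods and the questionnaire do not agree and should be reconciled.

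A reader might infer a biased treatment effect. That is not supported: leaving out strata or a baseline constraint does not bias the estimate, and omitting prognostic strata tends, if anything, to make the test conservative. The change is worth making because it is nearly free, not because the planned analysis would be invalid.

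**What to change.** In Statistical methods {20a}, or the analysis plan if one exists, before the group codes are opened:

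1. State that T0 means are constrained equal across arms, or that T0 is a covariate, and that arm contrasts are taken at T1 and T2. The constrained form keeps every randomized participant with a T0 value, which suits the intention-to-treat definition.
2. Include psychiatric medication and fibromyalgia as fixed effects. The reason is that they are randomization strata; little extra precision should be expected.
3. Either list time since last chemotherapy as a recorded variable and add it as a covariate, or withdraw the Discussion's statement that the effect of time is expected to be controlled.
4. Optionally, replace the baseline significance tests with the descriptive table alone. This is a reporting change.

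The cost is a few lines of text, a few degrees of freedom, and one date from the clinical histories already consulted for eligibility.
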